#### Multi-omics Data Integration

To integrate multi-omics features spanning genomic, transcriptomic, and spatial proteomic dimensions, we implemented the Cluster-of-Clusters Analysis (COCA) algorithm-a framework previously established in The Cancer Genome Atlas (TCGA) for identifying pan-cancer molecular subtypes.^[31, 32, 33, 34]^ The analytical workflow proceeded through three key phases:

First, individual omics platform clusters were derived through unsupervised t-SNE embedding, generating platform-specific sample groupings. These discrete cluster assignments were subsequently transformed into binary indicator matrices, where rows represented samples and columns encoded binarized cluster memberships. Second, we performed consensus clustering on the concatenated multi-omics matrix using a dynamic feature weighting approach. The optimal number of stable subgroups was determined by maximizing the average silhouette width across k = 2 to k = 10 through Monte Carlo cross-validation (*n* = 1000 iterations). Finally, to quantify the relative contribution of each datatype to integrative classification, we systematically evaluated all pairwise combinations using the same COCA framework. Cross-datatype cluster concordance was assessed *via* Adjusted Rand Indices (ARIs), with values > 0.65 considered strong biological agreement.

### Machine learning model development and validation

The patients recruited in the first phase of this study will be randomly divided into training set, test set and validation set according to the ratio of 6: 2: 2. Considering the “events per variable” (EPV) rule, we apply the following steps to develop a robust recurrence prediction model. First, we will not treat all molecular features as separate predictors. Instead, we will compute summary metrics to reduce dimensionality (see section 5.1). Then Least Absolute Shrinkage and Selection Operator (LASSO) regression will be applied within the training subset to identify the most informative predictors, where the penalty parameter will be selected *via* grid search in nested 5-fold cross-validation. This procedure typically yields less than 9 variables, satisfying EPV≥10 given an expected 80 events (26.7% of the 300 patients).

All parameter tuning will be confined to the training set to avoid information leakage. Machine learning-based classifiers will be implemented on the training set with 1000 rounds of ten-fold cross validation. In each round, the training set will be split into 10 subsets (folds); in each fold, a model will be trained on nine of the subsets and then validated on the remaining subset to tune the hyperparameters. Then we will apply all obtained models to the test set and compare the performance measurements. The optimal method will be used to construct the final model. The tested algorithms included: adaptive boosting (AdaBoost), decision tree, logistic regression, linear support vector machine (Linear SVM), radial basis function kernel support vector machine (RBF SVM), naive Bayes, nearest neighbors, neural net, quadratic discriminant analysis (QDA), random forest, and extreme gradient boosting (XGBoost). All machine learning algorithms have a solid research foundation.^[35]^

We will assess C statistics (area under the receiver-operator characteristic curve [ROC-AUC]), calibration, and clinical utility (decision-curve analysis) in the validation and test set. Finally, we determined an algorithm for developing predictive models, which has been widely popularized in the machine learning community and has excellent scalability, high running speed and state-of-the-art accuracy. It has better average performance than other algorithms in tests. Therefore, it is chosen for further optimization. The model willed be externally and respectively validated on two additional cohorts of NSCLC patients from published database^[10,11]^ and subsequent phases of the CLEVER study to confirm reproducibility and generalizability. If necessary, we will recruit a multi-center prospective multi-region cohort from collaborating institutions of medical alliance for further verification.

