In our preliminary retrospective investigation of 81 patients with stage I NSCLC (Chinese PKUPH cohort, named CHN-P), we observed that there are strong ancestry disparities in lung cancer and Asian NSCLCs exhibit diverse genomic features. Regrettably, only a small number of patients, all of whom were at stage I, and the multi-region sampling methods were not consistent.^[12]^ To deepen our understanding of intratumoral heterogeneity in Chinese lung cancer patients, we expanded our study to include patients with stage I-IIIA NSCLC and implemented a standardized multi-region sampling process. This approach not only allowed us to explore the molecular signatures and clonal evolution inside tumors but also enabled us to investigate the immune microenvironment in the marginal zone and normal lung tissue. By uncovering the evolutionary molecular mechanisms and changes in the immune microenvironment from normal to aggressive borderline to tumor, we aim to provide valuable insights for clinical diagnosis and treatment strategies of lung cancer. With the prevalence of neoadjuvant therapy and its limited clinical benefits, there is a growing interest in identifying biomarkers and immune characteristics that are related to therapeutic efficacy. Hu *et al*. mapped tumor microenvironment changes during neoadjuvant immunotherapy by utilizing single-cell sequencing on tumor and peripheral blood samples and identified FCRL4+FCRL5^+^ B cells, CD 16^+^CX3CR1^+^ monocytes, and plasma estrogen changes as novel biomarkers.^[13]^ Xia *et al*. found a positive correlation between TYROBP expression and favorable responses to neoadjuvant camrelizumab, which was associated with increased infiltration of CD8^+^ T cells and enhanced effector responses of natural killercells.^[14]^ However, there have been no studies employing multi-region sampling cohorts for multi-omics research to explore the association of tumor heterogeneity with neoadjuvant efficacy and long-term survival. This study addresses this gap by innovatively collecting multi-region samples post-neoadjuvant therapy to investigate spatial regression patterns of tumors and changes in intratumoral heterogeneity. Furthermore, we have integrated various advanced spatial omics technologies to gain a more comprehensive understanding of the molecular landscape under neoadjuvant therapy.

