## Study design and highlights

We conduct a prospective large-scale multi-region Chinese lung cancer cohort called CLEVER study from Peking University People’s Hospital. The cohort is divided into two subcohorts: the naïve cohort, which includes patients who have not received neoadjuvant therapy before surgery, and the neoadjuvant cohort, which includes those who have. During surgery, samples of tumor tissue, marginal tissue, and matched normal tissue are collected. These samples undergo comprehensive multidimensional omics analyses, including whole exome sequencing (WES), RNA sequencing (RNA-seq), single-cell sequencing, and multiple spatial omics techniques such as Stereo-seq, digital spatial profiling (DSP), and imaging mass cytometry (IMC). Additionally, preoperative blood samples are collected on the morning of the surgery, and postoperative blood samples are collected during a two-year follow-up period for longitudinal dynamic monitoring of minimal residual disease (MRD) (Figure 1A). The primary endpoint of the study are two-year disease-free survival (DFS) and overall survival (OS). The secondary endpoint is to identify available predictors of clinical benefit.

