##### Consideration for recurrence prediction validation

In this study, we aim to validate a machine-learning-based lung cancer recurrence prediction model with anticipated sensitivity of 90% ± 10% and specificity of 90% ± 10%. To calculate the necessary sample size for this diagnostic validation, we anchor our calculations to a fixed two-year recurrence (event) rate of 20%, based on retrospective study of recurrence after complete resection of early NSCLC.^[17, 18]^

Using Buderer’s formula for sensitivity and specificity sample size estimation:^[19, 20]^

$$N=\frac{Z^{2}\cdot p(1-p)}{d^{2}\cdot \text{ Prevalence }}=\frac{(1.96{)}^{2}\cdot 0.9\cdot 0.1}{0.1^{2}\cdot 0.2}\approx 173\text{ patients }$$

Here p is the anticipated sensitivity or specificity (0.90), d is the half-width of the 95% confidence interval (0.1), and Prevalence is the event prevalence (0.25). This calculation yields approximately 173 patients required to estimate sensitivity and specificity with ±10% precision at α = 0.05.

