#### Inclusion and exclusion criteria

##### Inclusion Criteria

(1) Age ≥ 18 years old; (2) Stage I-IIIA operable NSCLC (ninth AJCC); (3) Sufficient tumor tissue and blood sample with a suspected tumor with a short diameter of at least 15 mm on the preoperative image; (4) NSCLC was confirmed by histopathology, and clinical, imaging and follow-up data were available; (5) Eastern Cooperative Oncology Group (ECOG) Performance Status of 0–1; (6) Written informed consent.

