#### Patient management

In the CLEVER study, all eligible patients are presented at a weekly multidisciplinary tumor board meeting. Decisions regarding neoadjuvant therapy versus upfront surgery are made by consensus based on published authoritative guidelines, taking into account tumor stage (II–IIIA generally considered for neoadjuvant), resectability, and patient preference. Once the treatment plan is determined, research staff obtain written informed consent from participants in the hospital room. The following two questions are explained in detail to ensure that patients fully understand. First, this study involves repeated blood sampling of eight scheduled time points over two years. Potential risks (*e.g*., transient pain, bruising, hematoma, infection) are described, and standard phlebotomy precautions are assured. Second, this study involves a two-year follow-up schedule, including clinical visits and imaging studies. Patients are informed of data confidentiality measures and their right to withdraw at any time without affecting clinical care. Patients treated with direct surgical resection belongs to the Naïve cohort while those undergoing surgical resection following neoadjuvant immunotherapy belongs to the Neoadjuvant cohort). For patients assigned to the neoadjuvant cohort, the consent form includes additional sections that explain the risk and benefit from the neoadjuvant therapies. Participants have the opportunity to ask questions and are provided contact information for study coordinators and the ethics committee. Comprehensive clinical information is collected from all participants, including age, gender, smoking history, radiological image characteristics, and histopathology descriptions.

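### One recurrence model pools naïve and neoadjuvant patients across stages I–IIIA and is judged on pooled measures, so its AUC may partly restate stage and treatment

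*Protocol article*

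**What the plan says.** Four parts of the protocol article bear on this.

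- **Who enters the model.** The section *Machine learning model development and validation* opens by stating this: "The patients recruited in the first phase of this study will be randomly divided into training set, test set and validation set", in a 6:2:2 ratio. No stratification factor is named. One final model is chosen from eleven algorithms after LASSO selection among summary metrics from the multi-omics integration.
- **Who those patients are.** *Study design and highlights*: "The cohort is divided into two subcohorts: the naïve cohort, which includes patients who have not received neoadjuvant therapy before surgery", the other subcohort being patients who have. Eligibility covers "Stage I-IIIA operable NSCLC (ninth AJCC"). *Patient management* says the choice between neoadjuvant therapy and upfront surgery is made "taking into account tumor stage (II–IIIA generally considered for neoadjuvant), resectability, and patient preference". Treatment is therefore linked to stage, but not one-to-one.
- **How the model is judged.** The same machine learning section lists AUC, calibration and decision-curve analysis in the validation and test sets. It names no breakdown by subcohort or stage and no reference model. The model is then to be "externally and respectively validated on two additional cohorts of NSCLC patients from published database" and in later CLEVER phases, with a multi-centre cohort if necessary.
- **Where imbalance is handled.** *Confounding bias correction* sets out matching, covariate adjustment and subgroups by stage and ECOG. All of it is tied to comparing the neoadjuvant and naïve cohorts, with DFS and OS as the modelled outcomes. None is linked to the prediction model.

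**The concern.** Tissue is sampled at surgery. In the naïve subcohort the features describe untreated tumour. In the neoadjuvant subcohort they describe what therapy has left, and the *Introduction* makes therapy-related change in intratumoral heterogeneity a study question. The plan thus expects treatment to alter features that the model uses as if they meant the same thing in everyone. Cluster-type summaries from the multi-omics integration could also simply encode treatment or stage.

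A pooled AUC counts every pair of a patient with and a patient without recurrence, including pairs from different strata. Ranking those pairs correctly may need nothing beyond stage or treatment history, which the tumour board has before any sequencing. Without a reference model, a reader cannot tell how much of the reported accuracy the molecular work adds. Without results by subcohort, a reader cannot tell whether the model works in neoadjuvant patients.

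**Working it through.** **The plan's own figures.** The validation calculation reproduces: 1.96² × 0.9 × 0.1 / (0.1² × 0.20) = 172.87, so 173; and 173 / 0.6 = 288.3, so 289. The event count for modelling reproduces: 80 / 300 = 26.7%. None of these figures is divided by stage or subcohort.

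**Set sizes with 300 patients.** Training 0.6 × 300 = 180, with 0.6 × 80 = 48 expected events. Test set 0.2 × 300 = 60, with 0.2 × 80 = 16 events (12 at a 20% rate, 15 at 25%).

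**AUC of a stage indicator alone.** Let w be the share in the higher-risk stratum, r1 and r0 the event rates in the higher and lower strata, and e = w·r1 + (1 − w)·r0. Then

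TPR = w·r1 / e, FPR = w·(1 − r1) / (1 − e), AUC = 0.5 + (TPR − FPR) / 2.

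The shares and stratum rates below are assumptions, because the article gives none.

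1. *w = 0.5, e = 25%, stage hazard ratio 2.* With S the lower stratum's two-year DFS, S + S² = 1.5, so S = 0.823, r0 = 17.7% and r1 = 32.3%. TPR = 0.646, FPR = 0.451, AUC = **0.597**. (The article's hazard ratio of 2 is for high- against low-risk groups; using it for stage is an assumption.)
2. *w = 0.5, r0 = 12%, r1 = 38%.* TPR = 0.19 / 0.25 = 0.760, FPR = 0.31 / 0.75 = 0.413, AUC = **0.673**.
3. *Equal rates.* TPR = FPR, AUC = **0.50**.
4. *Wider grid.* With w from 0.2 to 0.5 and rates of 15/30%, 15/40% or 20/40%, the AUC is 0.58 to 0.66. Holding the overall rate at 26.7% with 15–20% in the lower stratum gives 0.59 to 0.74.

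**Effect on a model with real molecular signal.** In a simulation with a normally distributed marker whose AUC is 0.70 inside each stratum, combined optimally with the stratum's risk, the pooled AUC is 0.73 (w = 0.3, 15% against 30%) and 0.76 (w = 0.4, 15% against 40%).

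**What subgroup reporting can deliver.** If 20–50% of patients are neoadjuvant, the test set holds 60 × 0.2 = 12 to 60 × 0.5 = 30 of them. At a 30% share the expected number is 18. Under an unstratified draw of 60 from 300, its standard deviation is √(60 × 0.3 × 0.7 × 240/299) = 3.2, so roughly 12 to 24 could fall in the test set. Stratifying removes that variation.

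**The case against.** **Omission rather than error.** Candidate predictors, benchmarks and subgroup performance are often left to a fuller document, nothing bars stage from the LASSO candidates, and a prognostic model may properly use stage. This stands in part: the article does not claim superiority over stage. But it fixes the split, selection method, algorithms, performance measures and validation datasets, and in that detail commits to one pooled model.

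**A stage-only model would be noticed.** The plan anticipates sensitivity and specificity of 90%; a classifier reaching both has an AUC of at least (0.9 + 0.9) / 2 = 0.90, well above 0.60–0.67. A model carrying stage alone would indeed fall visibly short. However, the 90% figures are sample-size inputs, and the machine learning section makes them no acceptance threshold. The realistic case is a model with some molecular signal whose pooled figure cannot be taken apart.

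**Stronger readings that the document does not support.**
- *The published external cohorts contain no treated patients.* The article does not give their treatment status. Its remark that "there have been no studies employing multi-region sampling cohorts for multi-omics research to explore the association of tumor heterogeneity with neoadjuvant efficacy" makes neoadjuvant content unlikely, but concerns what was studied, not who was enrolled.
- *External validation cannot reach neoadjuvant patients.* Later CLEVER phases are also named and would include them if the two-subcohort design continues.
- *The contrast is untreated stage I against treated stage II–IIIA.* Stage II–IIIA is only generally considered for neoadjuvant therapy, and matching on clinical stage presupposes overlap.
- *The planning rate proves the problem.* The article says "we anchor our calculations to a fixed two-year recurrence (event) rate of 20"%, "based on retrospective study of recurrence after complete resection of early NSCLC". That neoadjuvant patients were absent from that source is an inference, and a sample-size prevalence has no bearing on whether a pooled AUC reflects stage.

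**Conclusion.** The concern holds in limited form. The article states an unstratified split and a single model over two subcohorts whose tissue features differ by treatment exposure. It judges that model on pooled measures and does not carry its own stage and cohort adjustment over to it. If recurrence differs by stage or subcohort, and if the predictors carry that information, the pooled AUC is partly what is already known clinically.

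On the two main illustrations, stage alone accounts for an AUC of about 0.60–0.67, and pooling lifts a within-stratum 0.70 to about 0.73–0.76. These rest on assumed shares and rates; with equal rates there is no effect, and the true size cannot be fixed from the article. The finding is that the molecular gain and the performance in neoadjuvant patients would not be visible, not that the model is invalid in them. A change is worth making before the model is fitted.

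**What to change.** 1. Stratify the 6:2:2 split by subcohort, and by stage where numbers allow.
2. Fit a reference model with clinical stage and subcohort only, in the same training set. Report the recurrence model's gain over it in AUC, calibration and net benefit.
3. Report performance separately for naïve and neoadjuvant patients with confidence intervals, labelled descriptive.
4. Claim external validity for neoadjuvant patients only from datasets shown to include them, for example later CLEVER phases, and state the treatment composition of the published cohorts.

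Forcing stage and subcohort into the recurrence model is optional: with about 48 training events, two correlated terms take up scarce capacity, and the reference model answers the main question without them.

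The cost is protocol wording, one small extra model and additional tables; no new patients or assays are needed. Subgroup estimates will be imprecise, with about 16 events in the whole test set, and the gain over stage may look less favourable than the pooled AUC.

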##### Consideration for survival analysis

In the first phase of the CLEVER study, we aim to compare 2-year DFS between predefined high-risk and low-risk groups using a two-sided log-rank test at α = 0.05 and 80% power (1-β = 0.80). Based on our preliminary data (CHN-P cohort),^[12]^ we assume a 2-year DFS event (recurrence or death) rate of 25% in the overall population. We further posit that the high-risk group will experience a hazard ratio (HR) of 2.0 relative to the low-risk group.

Applying the Freedman formula for survival comparisons:^[16]^

$$N_{\text{events }}=\frac{{\left(Z_{1-\frac{\alpha }{2}}+Z_{1-\beta }\right)}^{2}}{(\ln HR{)}^{2}}=\frac{(1.96+0.84{)}^{2}}{(\ln2{)}^{2}}\approx 43\text{ events }$$

Assuming a 25% event rate, at least 172 patients are needed to observe the required number of DFS events.

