##### Consideration for machine learning modeling

The novel lung cancer recurrence prediction model will be constructed based on machine-learning algorithms (section 5.2). For the model development, we adopt a ratio of 6:2:2 for the training, validation, and test sets. This division ratio is based on the consideration that 60% training provides adequate data for model fitting and feature selection, while 20% validation allows unbiased hyperparameter tuning, and 20% test ensures a fully held-out assessment to guard against overfitting. This ratio balances model complexity and evaluation rigor, as recommended for medium-sized cohorts.^[21, 22, 23]^ When 173 patients are recruited for statistical power in the training set, a total of 289 cases are required.

In summary, to address the above three dimensions of statistical consideration and the disruption caused by loss to follow-up, we plan to enroll 300 patients in the first phase. This provides sufficient power for survival analysis while also accommodating downstream modeling requirements.

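### The EPV≥10 claim counts 80 events from all 300 patients, but LASSO selection uses only the 180-patient training set, where eight variables give an EPV of 6.0 at the plan's own event rate

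*Protocol article*

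**What the plan says.** All references are to the Protocol article. Under Consideration for machine learning modeling, the first-phase size is fixed: "we plan to enroll 300 patients in the first phase". Under Machine learning model development and validation, these patients "will be randomly divided into training set, test set and validation set according to the ratio of 6: 2: 2". LASSO "will be applied within the training subset to identify the most informative predictors", and the next paragraph adds: "All parameter tuning will be confined to the training set to avoid information leakage". The EPV statement follows the LASSO step directly: "This procedure typically yields less than 9 variables, satisfying EPV≥10 given an expected 80 events (26.7% of the 300 patients".

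Two other event rates bear on the same count. For the prediction model, Consideration for recurrence prediction validation says "we anchor our calculations to a fixed two-year recurrence (event) rate of 20" (per cent). For the survival comparison, Consideration for survival analysis says "we assume a 2-year DFS event (recurrence or death) rate of 25% in the overall population". The Sample size calculation section anticipates a recurrence proportion between 15% and 30%. The article gives no derivation for 26.7%.

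**The concern.** EPV describes the data on which predictors are selected and a model is fitted. The 120 patients in the validation and test sets contribute no events to the LASSO step, yet their events are in the 80. The stated denominator is all 300 patients, so the base is not in doubt.

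The recurrence model is one of the study's declared aims, and the section introduces the EPV rule as part of making that model robust. If the rule is not met at the stated number of variables, a reader will think that selection rests on more information than it does. The article is also inconsistent in its approach. Its sample-size section reasons from the training set, requiring 173 patients there and scaling up to a total of 289, whereas the EPV sentence reasons from the total.

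**Working it through.** **Inputs**
- First-phase enrolment: 300 (Consideration for machine learning modeling).
- Training share: 6 parts in 10 (Machine learning model development and validation).
- Variables: fewer than nine, so at most eight (same section).
- Event rates: 26.7% (same section), 25% (Consideration for survival analysis), 20% (Consideration for recurrence prediction validation), and an anticipated range of 15% to 30% (Sample size calculation).

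**Formula:** EPV = (patients × event rate) / number of variables.

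**The plan's own figure.** 80/300 = 26.7%, and 80/8 = 10.0. It reproduces, but only with all 300 patients as the base.

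**The same calculation in the training set.** 0.6 × 300 = 180 patients.

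| Event rate | Training events | EPV with 8 variables | Most variables with EPV≥10 |
|---|---|---|---|
| 15% | 27 | 3.4 | 2 |
| 20% | 36 | 4.5 | 3 |
| 25% | 45 | 5.6 | 4 |
| 26.7% | 48 | 6.0 | 4 |
| 30% | 54 | 6.75 | 5 |

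**What the claim would need.** For 80 events among 180 patients, the event rate would have to be 80/180 = 44.4%, well above the anticipated maximum of 30%. Alternatively, 80 training events at a 60% share would need 80/0.267/0.6 ≈ 500 patients in total at 26.7%, or 80/0.20/0.6 ≈ 667 at 20%.

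**Separating the two sources of shortfall.** Correcting the base alone, at the plan's 26.7%, takes the EPV from 10.0 to 6.0. Changing the rate alone, on all 300 patients, gives 60/8 = 7.5 at 20% and 75/8 = 9.4 at 25%. The wrong base is the larger of the two, and 4.5 is the result of both together.

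**The case against.** **Eight is a ceiling.** LASSO may keep fewer variables. With five, the training-set EPV is 36/5 = 7.2 to 48/5 = 9.6. With three at 20% it is 36/3 = 12, and with four at 26.7% it is 48/4 = 12. This stands: 4.5 to 6 is the EPV at the ceiling, not a forecast for the final model. But the article asserts EPV≥10 for anything below nine, and 80/8 is the bound on which the assertion rests.

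**The 20% rate was set for another purpose.** It belongs to a precision calculation for sensitivity and specificity. This is fair, and the base error does not need it, since the plan's own 26.7% already gives 6.0. It is still a rate stated for the same prediction model, so it marks a reasonable lower case.

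**The final model might be refitted on more data.** The article does not say which patients are used to build the final model after the best algorithm is chosen, so a refit on all 300 is not excluded. The EPV sentence, however, is attached to LASSO selection, which is expressly limited to the training subset. Even a refit on all 300 would reach 10 with eight variables only if the event rate were about 26.7% or more.

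**There are other protections.** The plan reduces features to summary metrics, penalises, uses nested cross-validation, keeps held-out data, assesses calibration and plans external validation. A reader might infer from the low EPV that the model will be overfitted and miscalibrated, or that the plan has no safeguard against overfitting. The document supports neither reading. EPV≥10 is a rule of thumb, a low value raises the risk without determining the result, and the listed steps remain in place. They do not make the EPV sentence correct.

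**Selected versus candidate variables.** EPV could also be counted on all candidates screened, which would lower it further. The article gives no number of candidates, so this cannot be quantified, and the point does not depend on it.

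**Conclusion.** The EPV≥10 statement is wrong as written. With eight variables in the 180-patient training set, EPV is 6.0 at the plan's 26.7%, 5.6 at 25% and 4.5 at 20%. No rate in the anticipated 15% to 30% range takes it above 6.75. EPV≥10 would hold with at most four variables at 25% to 26.7%, and three at 20%.

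These figures assume full enrolment of 300, an exact 60% training share, events spread in proportion across the three sets, and no loss to follow-up. Losing the full 10% that the plan tolerates would leave 162 training patients and an EPV of 162 × 0.267/8 = 5.4 at 26.7%, or 162 × 0.20/8 = 4.1 at 20%. That is a limiting case, and the plan also provides for multiple imputation.

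The consequence is a higher risk of overfitting than the text implies. The error does not affect the 300-patient target, which the article builds up from 173/0.6 and an allowance for loss, or the primary endpoints of two-year DFS and OS.

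**What to change.** Recompute EPV from the events expected in the training set, at one event rate reconciled across the sections that now use 20%, 25% and 26.7%. Then choose one of two courses:

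1. Keep the EPV≥10 rule and cap the number of selected predictors at what the training set supports: four at 25% to 26.7%, three at 20%.
2. Withdraw the EPV≥10 claim, state the actual value (about 4.5 to 6 for eight variables), and report optimism-corrected performance and calibration for whichever algorithm becomes the final model. Calibration in the validation and test sets is already planned, so the optimism correction is the addition.

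The remedy should not depend on keeping LASSO's shrunken coefficients. LASSO serves here to select features, and eleven classifiers are then compared, several of which have no such coefficients.

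The cost is a sentence or two of text and possibly a smaller model. No additional patients or data are needed.

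### The test set is called held out but is used to choose among eleven algorithms, so the selected model's test-set performance will be optimistic, and no other internal set is clearly reserved

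*Protocol article*

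**What the plan says.** Two sections of the protocol article assign roles to the three parts of the first-phase cohort.

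- *Consideration for machine learning modeling* sets the 6:2:2 split. For the validation part, "20% validation allows unbiased hyperparameter tuning". For the test part, "20% test ensures a fully held-out assessment to guard against overfitting".
- *Machine learning model development and validation* repeats the split (patients "will be randomly divided into training set, test set and validation set according to the ratio of 6: 2: 2") and then describes a different flow. On tuning: "All parameter tuning will be confined to the training set to avoid information leakage". On comparing algorithms: "Then we will apply all obtained models to the test set and compare the performance measurements". On selection: "The optimal method will be used to construct the final model".

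The last paragraph of the second section says that discrimination (AUC), calibration and decision-curve analysis are assessed in both the validation and the test set. It says of the chosen algorithm: "It has better average performance than other algorithms in tests". It also plans external validation in two published cohorts and in later CLEVER phases. No optimism correction and no further held-out set are described.

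**The concern.** The test set has two incompatible jobs. The design section makes it the untouched check, while the analysis section makes it the place where candidate algorithms compete. The highest of several noisy AUCs exceeds, on average, the true AUC of the model that produced it. Reporting that value as a held-out result overstates how well the model discriminates, and calibration and decision curves for the selected model come from the same patients.

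The second inconsistency removes the obvious fallback. If tuning stays in the training set, the validation set is untouched and could supply the honest internal estimate. The design section, however, gives the validation set to tuning. An analyst who follows the design section for tuning and the analysis section for selection will have used both 20% sets before reporting on either.

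Recurrence prediction is one of the study's stated aims, and the internal test-set result is what the article offers as protection against overfitting. The survival endpoints (two-year DFS and OS) are not touched by this point.

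**Working it through.** **1. The plan's own figures.** The validation sample size is 1.96² × 0.9 × 0.1 / (0.1² × 0.2) = 172.9, so 173, as stated. The total for a training set of 173 is 173 / 0.6 = 288.3, rounded up to 289, as stated. The plan rounds up to 300. Both figures reproduce.

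**2. Size of each set.** 300 × 0.6 = 180 for training, and 300 × 0.2 = 60 each for validation and test.

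**3. Events in the test set.** The analysis section expects 80 events in 300 (26.7%), so 80 × 0.2 = 16. At the 20% rate used in *Consideration for recurrence prediction validation*, 60 × 0.2 = 12.

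**4. Number of candidates.** The list has AdaBoost, random forest, XGBoost, a decision tree, logistic regression, two support vector machines, naive Bayes, nearest neighbours, a neural net and QDA. That is 11. One model per algorithm is taken here.

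**5. Size of the selection effect.** The documents give no figure, so it was simulated with 4000 runs per setting.

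- Each of 11 models gives binormal scores with the same true AUC. The mean shift in patients with events is √2 × Φ⁻¹(AUC).
- Within each patient the 11 scores share a common part, score = shift + √ρ × common + √(1 − ρ) × own, so any two models correlate at ρ.
- With n₁ events and n₀ = 60 − n₁ non-events, AUC = (rank sum of events − n₁(n₁ + 1)/2) / (n₁ n₀).
- The model with the highest test AUC is selected. Its test AUC is recorded, and so is its AUC in a second, untouched set of 60.

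True AUC (0.70, 0.80, 0.90), ρ (0 to 0.9) and equal model quality are assumptions. Mean inflation of the selected test AUC:

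| Events | True AUC | ρ = 0 | ρ = 0.5 | ρ = 0.8 | ρ = 0.9 |
|---|---|---|---|---|---|
| 16 | 0.70 | 0.115 | 0.085 | 0.057 | 0.039 |
| 16 | 0.80 | 0.094 | 0.072 | 0.049 | 0.035 |
| 16 | 0.90 | 0.061 | 0.049 | 0.035 | 0.026 |
| 12 | 0.70 | 0.126 | 0.094 | 0.064 | 0.047 |
| 12 | 0.80 | 0.103 | 0.078 | 0.054 | 0.039 |
| 12 | 0.90 | 0.066 | 0.053 | 0.038 | 0.027 |

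With 16 events and ρ of 0.8 to 0.9 the inflation is 0.026 to 0.057. The largest value, for independent models and 12 events, is 0.126. In the untouched set the selected model's mean AUC was within 0.002 of the true value in every setting, so the excess comes from selecting and scoring on the same patients.

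**6. Roles side by side.**

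| Set | Design section | Analysis section |
|---|---|---|
| Training | Fitting, feature selection | Fitting, feature selection, all tuning |
| Validation | Tuning | Performance reporting only |
| Test | Held-out assessment | Comparison and choice of algorithm, then performance reporting |

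The validation and test rows cannot both be right as written.

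**The case against.** The strongest reply is that the analysis section, read alone, describes a workable scheme: train and tune on 60%, select on the test set, then assess on a validation set used for neither. The article would then only have swapped two labels, and the validation-set result would be clean. That reading is possible, and it limits the point to the test-set figure. It does not remove the point, because the design section gives the validation set to tuning and claims held-out status for the test set.

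External validation is also planned in cohorts that play no part in selection, so claims of generalisability do not rest on the internal figure alone. That stands too, but it does not correct the internal figure.

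The size is open to challenge. Equal model quality favours a large bias, and models built on the same few predictors are likely to be highly correlated, which points to the lower end of the range.

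A reader might infer more than the text supports:

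- *That all reported performance is biased, or that the validation set has no role.* The analysis section gives the validation set a reporting role, and under that section its result would be unbiased.
- *That LASSO selection before the folds inflates the reported results.* Cross-validation is used there for tuning, and no cross-validated AUC is planned as a performance claim. LASSO is confined to the training data and does not contaminate the other sets.
- *That sensitivity and specificity are inflated.* The 90% values are planning assumptions. The model section names AUC, calibration and decision curves for the validation and test sets, not sensitivity or specificity.
- *That the sentence on average performance in tests confirms selection on the test set.* It is ambiguous and is not needed, since the comparison on the test set is stated outright.

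**Conclusion.** The concern holds for the internal test-set performance of the selected model. The article calls the test set held out, uses it to choose among eleven algorithms, and reports performance on it. The inflation in AUC is roughly 0.03 to 0.06 with 16 events and highly correlated models, and up to about 0.13 with independent ones. These sizes assume equally good algorithms, one model per algorithm, a true AUC of 0.70 to 0.90 and a 60-patient test set. A clearly superior algorithm would reduce them.

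Separately, the two sections contradict each other on where tuning is done, so no internal set is unambiguously reserved for an unbiased assessment. The external cohorts and later CLEVER phases are not affected.

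**What to change.** Choose the algorithm before the test set is opened, in one of two ways:

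- by nested cross-validation within the training set, with LASSO selection repeated inside each fold, because cross-validation would then be the selection criterion; or
- on the validation set, whose result is then no longer presented as held out.

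The first draws on more information: 80 × 0.6 = 48 expected events in training, against 80 × 0.2 = 16 in the validation set. Then lock one model and score it once on the test set. Reword both sections, including the paragraph on performance reporting, so that each set has one role throughout.

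If the sponsor prefers to keep selection on the test set, the alternative is to confine tuning to the training set, report the untouched validation set as the held-out assessment, and drop that claim for the test set.

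The cost is wording and some computing time, with no extra patients. The reported internal AUC will probably be slightly lower. The choice has to be made before the test data are examined, because their independence cannot be restored afterwards.
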